## Abstract

**Introduction::**

Clinical ultrasound is a technique that increases diagnostic capacity and facilitates clinical decision making. The objective is to develop and validate an ultrasound training methodology oriented to the clinical practice of the family physician.

**Methods::**

Quasi-experimental study, with a before/after design, a control group, and 1 year of follow-up. Twenty family physicians working in primary care health centers with a list of over 800 patients will be included, as well as a control group of family physicians with similar characteristics in terms of age, sex, and patient list. A structured training process oriented to the clinical practice of the family physician, primary care clinical ultrasound classroom (AECAP), will be carried out, and the improvement of knowledge and skills of the participants will be evaluated, as well as the improvement of the quality of care based on clinical indicators.

**Discussion::**

The family physician is in a privileged situation allows increasing the performance of ultrasound in frequent clinical situations and reducing care hours. We hope that the results obtained in this study demonstrate the effectiveness of the structured training method (AECAP) and support the generalization of ultrasound in primary health care.

**Ethics and dissemination::**

The study was approved by the Medical Research Ethics Committee of Salamanca on December 17, 2018 (cod 2018 11 134). The trial was registered in ClinicalTrials.gov provided by the US National Library of Medicine-number: NCT04283383.

## Introduction

1

The use of ultrasound to aid the medical diagnosis poses an advancement in the diagnostic process, which facilitates and improves decision making in many areas of the usual clinical practice.^[1,2]^ The great possibilities of this technique, its innocuousness and its low cost, as well as its ease of use both in the doctor's office and at the patient's home, make it a first-line tool in the daily work of family physicians.^[2]^

The first publications that valued experiences and results of the use of ultrasound in primary care appeared in 1988 and refer to the training of doctors in obstetric ultrasound.^[3]^ From that point, a large number of studies have demonstrated that the use of ultrasound in the scope of primary care is a cost-effective diagnostic tool for multiple pathologies.^[4,5]^ Furthermore, its possibilities of use in family physician offices include a wide variety of clinical scenarios.^[6]^ Likewise, it has been demonstrated that, in some pathologies, whose paradigm could be cholelithiasis, the use of ultrasound by family physicians allows for an important reduction of care time.^[7]^ A specific use of ultrasound in family physician offices is the “point-of-care ultrasound” model (POCUS),^[8–10]^ which is characterized for focusing the technique on responding to a specific question, with brief examinations that guide ultrasound as a tool for clinical decision making and not only as a diagnostic test.^[11]^

Different studies show that, when this technique is performed by family physicians with enough training, the diagnostic findings for frequent pathologies are in line with those obtained by radiologists.^[12,13]^ Thus, there is a kappa index of over 0.8 for most pathologies,^[13,14]^ both in the diagnosis and in the follow-up of already diagnosed lesions.^[15]^ The worse levels of consistency have been reported in pancreatic and spleen pathology.^[13,16]^ Other studies have shown an increase of resolving capacity and a decrease of care time in certain processes and clinical scenarios, as well as a 50% decrease in referrals and applications for diagnostic tests.^[17,18]^

Therefore, multiple authors and scientific societies of primary care state that the generalized use of ultrasound in the usual practice of family physicians allows making clinical decisions with greater diagnostic precision and reducing the high levels of uncertainties with which these professionals work in the field of healthcare, as well as contributing to reducing the waiting lists of radiology services and shortening the care time in potentially critical situations.^[2,19,20]^

In the scope of primary health care in Spain, the use of ultrasound has been generalized in the healthcare centers of all the autonomous communities, which is also happening in other European countries.^[21]^ This is posing an important effort in the training of family physicians in the use of this tool. Currently, the ultrasound training offered by public and private entities for family physicians in Spain is abundant and of high quality, although it usually has a very academist orientation with little focus on the clinical practice.

The primary care clinical ultrasound classroom (PCCUC) presented by this project aims to provide the participating family physicians with specific training in ultrasound oriented to clinical practice in the scope of primary health care. The PCCUC uses a novel formative system characterized for the valuation and interpretation of clinical cases in real time (clinical session with the patient). Moreover, it includes a 1-year follow-up of the participants in order to assess the utility of this method not only in terms of the knowledge and skills acquired, but also regarding other results of clinical practice.

Therefore, the main objective of the project is to develop an ultrasound training methodology oriented to the clinical practice of family physicians in the scope of primary health care; it also aims to evaluate the effectiveness of such training regarding the increase of knowledge and skills and the improvement of the clinical practice, evaluated by the number of referrals to specialized radiology services, diagnostic waiting time, diagnostic precision, and improvement of the health care provided.

As a secondary objective, the project aims to validate the PCCUC training system for use in the training of undergraduates and post-graduates and in the continuous training of family physicians.

## Methods

2

### Design and scope

2.1

This is a quasi-experimental study with a before/after design, a group control and a 1-year follow-up to evaluate the effectiveness of the formative intervention in clinical ultrasound with family physicians. The control group will consist of family physicians with similar characteristics, who will not participate in the AECAP. The project will be carried out with family physicians who work in Spanish primary healthcare centers.

### Study population

2.2

The study will include 20 family physicians who want to participate voluntarily, meeting the following inclusion criteria: the practitioners must work in a Spanish primary healthcare center where ultrasonography is available and which belongs to the Health Service of Castilla y León (Sacyl) and to the Health Area of Salamanca; the participants must have a list of over 800 patients; they must have no previous training in clinical ultrasound; and they will have to sign a commitment of attendance and participation in the PCCUC. A control group will be recruited, which will be composed of physicians with similar characteristics in terms of age, sex, workplace, and number of patients assigned. They will be recruited in the first quarter of 2020.

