#### Formative methodology of the AECAP

2.3.2

The ultrasound classroom will be attended twice per month, specifically on the second and fourth Tuesday of each month, from 6 p.m. to 8.30 p.m. At the beginning of each AECAP, the participants will be given the necessary material to complete the ultrasound training individually, following the structure described below.

Basic course in clinical ultrasound (abdomen and thyroid ultrasonography) of a total duration of 30 hours (15 hours of theory and 15 hours of practice). The course will be taught in the first term of 2020.

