##### Clinical sessions with patients

2.3.2.1

In this stage, the participants will familiarize with the practical utility of clinical ultrasound through clinical cases with real patients, who agreed to participate by signing an informed consent document. The sessions will be presented as follows: before the patient enters the classroom, the clinical case is presented to the participating physicians, the patient enters the classroom, the ultrasound is carried out with visualization in the TV of the classroom, and the result is written in a report (Fig. 1). All the data will be incorporated to the “case presentation model.” This phase will be conducted from April to October 2020. The teacher of each session will collect the informed consent of the participating patients.

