###### Secondary results

2.3.2.3.2

Evaluation of results in the clinical practice.

-Number of applications to the radiodiagnosis service: the number of applications of abdominal and thyroidal ultrasound scans sent to the radiology service by the physicians in the PCCUC and those in the control group in the year before and the year after the training process will be studied.-Number of referrals to specialized health care: In the same annual periods, the number of referrals by both groups of family physicians will be valued.-Diagnosis waiting times of physicians of the intervention and control groups for 2 processes, which will be used as indicators of healthcare quality improvement (cholelithiasis and the etiological diagnosis of haematuria). The source of data will be the computerized clinical history of the Health Service of Castilla y León.

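### The criteria do not require the same patient list in the year before training, and the request and referral counts have no denominator, so part-year tenure or a change of list can blur or bias the secondary before/after comparison

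*Protocol article*

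**What the plan says.** **Eligibility (Protocol article, 2.2 Study population).** "The study will include 20 family physicians who want to participate voluntarily". They must work in a centre of the named health service and area that has ultrasonography, have no earlier ultrasound training, and meet the size rule "the participants must have a list of over 800 patients". The required undertaking concerns the course alone: "they will have to sign a commitment of attendance and participation in the PCCUC". Controls are to be "physicians with similar characteristics in terms of age, sex, workplace, and number of patients assigned". On timing: "They will be recruited in the first quarter of 2020". Time in post and continuity of the list are not mentioned for either group.

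**Training dates (2.3.2 and 2.3.2.1).** For the basic course: "The course will be taught in the first term of 2020". For the sessions with patients: "This phase will be conducted from April to October 2020".

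**Outcomes (2.3.2.3.2 Secondary results).** Abdominal and thyroid ultrasound requests from both groups "in the year before and the year after the training process will be studied". Referrals to specialist care are taken over the same two periods. Both are described as numbers, not as rates per assigned patient or per month in post.

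**Analysis (2.4 Data analysis).** For repeated quantitative before/after data the section names the paired t test or the Wilcoxon test. Two-group tests are listed separately. No between-group test of change is named.

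**The concern.** A before/after count is interpretable only if the physician was exposed to the same list for the same length of time in both years. The criteria do not secure this. A physician who took over a list of more than 800 patients in September 2019 meets every stated condition, yet has only about four months of requests on that list in 2019. A physician who changes list between the two windows brings a different denominator to each. In both cases the raw count changes although the training did nothing.

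The request and referral counts carry the study's evidence on clinical practice, which the Introduction makes part of the main objective. With 20 trained physicians, one or two such cases have visible weight. The trained group are volunteers, and controls are not selected on tenure, so nothing in the text makes the two groups equal in this respect.

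**Working it through.** The article gives no sample-size calculation, standard deviation, request rate or turnover figure, so there is no stated figure to reproduce. The steps below show the mechanism and a plausible range.

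**1. Length of the period.** Reading the first term as January to March, training starts between 1 January and 31 March 2020 and ends in October 2020. From the start of the year before to the end of the year after:
- start 1 January: 12 + 10 + 12 = 34 months;
- start 31 March: 12 + 7 + 12 = 31 months.

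**2. How likely is a change of list?** Assumption: annual turnover *t*, not in the article. P(change) = 1 − (1 − t)^(months/12), and P(at least one of 20) = 1 − (1 − P)^20.

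| Assumed turnover per year | P(change), 31 to 34 months | Expected among 20 | At least one |
|---|---|---|---|
| 3% | 0.076 to 0.083 | 1.5 to 1.7 | 79% to 82% |
| 5% | 0.124 to 0.135 | 2.5 to 2.7 | 93% to 95% |
| 10% | 0.238 to 0.258 | 4.8 to 5.2 | over 99% |

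**3. One part-year physician.** Assumptions: 5 requests per month, no training effect, four months in post in the year before, and the other 19 physicians with mean change 0 and SD of change 10.
- Before: 4 × 5 = 20. After: 12 × 5 = 60. Apparent change: +40.
- Shift of the group mean: 40/20 = +2, which is 2/60 = 3.3% of a full-year count.
- Sum of squares: 18 × 10² + 40² × 19/20 = 1800 + 1520 = 3320. SD = √(3320/19) = 13.2, so the standard error is about 32% larger than with an SD of 10.
- One-sample t from this case alone: 2/(13.2/√20) = 2/2.95 ≈ 0.68.

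This shift is upward, so it would hide a fall in requests.

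**4. Changes of list size.** At a constant rate per patient, the shift in the group mean is k × (ratio − 1)/20 for k physicians who change. Two moving to lists 30% smaller: 2 × (−0.3)/20 = −3%. Four: −6%. Two moving to lists 30% larger: +3%.

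**5. Both groups together.** Simulation with no training effect and 20,000 runs. Assumptions: 20 physicians per group (the control number is not stated), lists of 801 to 1,600, 0.04 requests per patient-year, Poisson counts, and for movers a new/old list ratio with the median shown and a log-scale SD of 0.25. Changes and SDs are percentages of the mean baseline count; rejection is at P < .05.

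| Movers, trained / control | Median list ratio | Change in trained group | Between-group difference in change | SD of that difference | Paired test rejects | Between-group test rejects |
|---|---|---|---|---|---|---|
| 0 / 0 | 1.0 | 0.0% | 0.0% | 6.5% | 5.1% | 5.1% |
| 20% / 20% | 0.8 | −3.5% | −0.1% | 7.4% | 8.8% | 4.7% |
| 20% / 20% | 1.2 | +4.6% | −0.1% | 8.5% | 8.7% | 5.0% |
| 20% / 0 | 0.8 | −3.5% | −3.4% | 7.0% | 9.0% | 7.6% |
| 0 / 20% | 1.2 | 0.0% | −4.8% | 7.6% | 5.1% | 8.1% |
| 30% / 10% | 0.7 | −8.3% | −5.6% | 7.7% | 26.3% | 10.8% |

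Equal moves leave the between-group contrast unbiased and only widen it. Unequal moves bias it. The within-group paired test is distorted whenever list sizes in the trained group drift in one direction.

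**The case against.** **The control group.** A reader might infer that every change of post is counted as a training effect. The documents do not support that. Counts are collected in both groups, and step 5 shows that equal changes cancel in a between-group contrast of change. What stands is that equality is not secured, and that for before/after data section 2.4 names within-group paired tests, which have no such protection.

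**When eligibility is checked.** It is tempting to say that eligibility is verified only once, at recruitment. The article dates recruitment but does not say when or how often the criteria are checked. The point rests only on the absence of a same-list condition.

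**Control similarity.** It covers age, sex and workplace as well as list size. Workplace partly covers a further scenario, a centre that acquired its scanner during 2019, because similar workplaces would tend to be affected alike. It does not cover personal tenure.

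**Newer physicians among the trained.** Physicians without earlier ultrasound training might be thought newer in post. Nothing in the article says so.

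**Direction and size.** The part-year example raises requests, so it masks a benefit and does not imitate one, and t ≈ 0.68 is far from significance. The Wilcoxon alternative would limit the influence of one extreme value. Both remarks are right. They reduce the weight of a single case but do not remove a bias shared by several.

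**A condensed article.** Rules for physicians who move, or a rate denominator, may be in a fuller document. That is fair for the analysis rules. But the inclusion criteria are set out explicitly here, and no later analysis plan can supply a year-before count on a list that the physician did not yet hold.

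**Acknowledged limitations.** Section 3.1 concedes that differences may not be due to the training alone. It neither names changes of post nor controls them.

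**Conclusion.** The point holds in limited form. The stated criteria allow physicians without a comparable year-before count, and the two count outcomes have no stated denominator to correct for it. The consequence is extra noise if the groups are affected equally. It is bias in either direction if they are not, or if the within-group test is used for inference.

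The actual size cannot be known from the article. On the assumptions shown, the bias in the between-group difference is about 3% to 6% of the baseline count when movers are unequal, with a false-positive rate of about 8% to 11% against a nominal 5%. The paired test reached 26% in the most unfavourable case. With equal movers, the SD of the difference rises from 6.5% to between 7.4% and 8.5%. All of this rests on assumed turnover, list ratios and request rates, and on an assumed control group of 20.

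Only the request and referral counts are affected. The primary knowledge and skills results are not, and no effect on the waiting times has been shown. This is worth correcting, but it does not undermine the trial.

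**What to change.** For the request and referral outcomes only, in both groups, adopt one of these:

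1. Require the physician to have held the same list since the start of the year-before window. This needs one check of administrative records at recruitment. It cannot govern moves after entry, so months in post in the year after should still be recorded.
2. Record months in post and list size in each window, and analyse requests and referrals per assigned patient over calendar months available in both windows.

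With either option, state that the effect estimate is the between-group difference in change. In the part-year example, matching months gives 4 × 5 = 20 requests in each window, a change of 0.

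**Cost.** Under option 1 a few recently appointed physicians leave the count comparison; under option 2 they contribute less to it. How many is not known, and with 20 trained physicians the loss of precision should be reported. They still take the course and count for the primary results, so the primary and count analyses may rest on slightly different sets of physicians, which should be stated. Option 2 keeps more physicians but does not remove differences in case mix between an old and a new list.

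### Controls need not be untrained in ultrasound, although the intervention physicians must be; this can dilute the between-group comparison of the secondary clinical-practice outcomes

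*Protocol article*

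**What the plan says.** All places are in the protocol article.

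- **Intervention group (section 2.2, Study population).** "The study will include 20 family physicians who want to participate voluntarily" opens the inclusion list. Among the criteria: "they must have no previous training in clinical ultrasound". The same list ends with "they will have to sign a commitment of attendance and participation in the PCCUC".
- **Control group (section 2.2).** A separate sentence describes "physicians with similar characteristics in terms of age, sex, workplace, and number of patients assigned". The Abstract (Methods) gives a shorter list: "a control group of family physicians with similar characteristics in terms of age, sex, and patient list".
- **Control group (section 2.1, Design and scope).** Controls are "family physicians with similar characteristics, who will not participate in the AECAP".
- **Where controls are used (section 2.3.2.3.2, Secondary results).** Radiology applications are studied "by the physicians in the PCCUC and those in the control group in the year before and the year after the training process". Referrals are counted over the same annual periods. Diagnostic waiting times for two processes are taken for both groups, with no period stated.
- **Tests (section 2.4, Data analysis).** The t test or Mann–Whitney for comparing groups, and the paired t or Wilcoxon for before/after data.
- **Background (section 1, Introduction).** "the ultrasound training offered by public and private entities for family physicians in Spain is abundant and of high quality". The sentence then qualifies this by calling such training academic in orientation, with little attention to clinical practice.

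**The concern.** Prior ultrasound training is the exposure under study. It is an entry rule for one group and is absent from the definition of the other. The inclusion list also demands a commitment to attend the classroom, so it cannot apply to controls as it stands. The sentence that does apply to them names the terms of similarity, and training is not one of them.

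The document itself makes trained controls plausible: it describes ultrasound as widespread in health centres and training as plentiful. Recruiters who follow the text could enrol controls who already scan.

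At stake is how a small between-group difference in requests, referrals or waits would be read. It could mean that the training changed little, or that some controls were already working in the way the training is meant to produce. Without a record of control training, the two could not be told apart.

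**Working it through.** **Step 1: is the gap closed elsewhere?** The control group is described in the Abstract, section 2.1, section 2.2 and, in passing, section 3.

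| Place | Terms for controls | Ultrasound training mentioned? |
|---|---|---|
| Abstract, Methods | age, sex, list | no |
| Section 2.1 | similar; not in the AECAP | only this course |
| Section 2.2 | age, sex, workplace, list | no |
| Section 3, Discussion | control group used to strengthen the results | no |

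Nothing requires controls to be untrained or records their training. The limitations (section 3.1) do not raise the point.

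**Step 2: which outcomes are exposed?** The knowledge tests, continuous evaluation, final case and six-patient examination (section 2.3.2.3.1) are described for participants only. Controls enter only the three secondary outcomes.

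**Step 3: effect on each possible analysis.** The document gives no effect size, standard deviation or control-group size, so there is no figure to reproduce. Let μ be the untrained mean, D the reduction produced by the training, f the share of controls trained before the study, and k the effect of their earlier training relative to D. Assume no other change over time.

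| Group | Year before | Year after | Change |
|---|---|---|---|
| Intervention | μ | μ − D | −D |
| Untrained controls | μ | μ | 0 |
| Already-trained controls | μ − kD | μ − kD | 0 |
| All controls | μ − fkD | μ − fkD | 0 |

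- *Year-after comparison:* (μ − fkD) − (μ − D) = D(1 − fk). With k = 1, f = 0.10, 0.25 and 0.50 leave 0.90, 0.75 and 0.50 of D. With k = 0.5, they leave 0.95, 0.875 and 0.75.
- *Difference in changes:* −D − 0 = −D for every f and k, so there is no dilution.
- *Paired test within the intervention group:* controls are not used, so there is no effect.

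**Step 4: does the plan secure the analysis that is immune?** Section 2.4 lists between-group tests and paired within-group tests, but no between-group test of change. For applications and referrals, the before-year data would at least allow one. For waiting times, no before period is stated.

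**Step 5: illustration of the loss of power.** Every input here is assumed except the 20 intervention physicians and the 0.05 level: 20 controls, a two-sided test, a year-after comparison, a standardised effect d, k = 1 and a common SD of 1. By the normal approximation, power = Φ(d(1 − f)·√(20/2) − 1.96).

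| f | d = 0.8 | d = 0.9 | d = 1.0 |
|---|---|---|---|
| 0 | 0.716 | 0.812 | 0.885 |
| 0.10 | 0.624 | 0.726 | 0.812 |
| 0.25 | 0.475 | 0.569 | 0.660 |
| 0.50 | 0.244 | 0.296 | 0.352 |

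For example, with d = 0.9 and f = 0.25: 0.675 × 3.162 − 1.96 = 0.174, and Φ(0.174) = 0.569.

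**The case against.** The best reply is that this is a before/after design with controls. Applications and referrals are collected for both years in both groups, so a stable difference from earlier training cancels once changes are compared. That is correct, as step 3 shows, and it limits the point. It does not dispose of it, because no comparison of changes is named and waiting times have no stated before period.

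Other replies also carry weight:

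- **Equal effect.** The Introduction regards existing courses as weakly tied to practice. Earlier-trained controls may therefore show less than the full effect (k below 1), and dilution would be smaller.
- **Condensation.** The full protocol may hold fuller control criteria. If it does, one sentence settles the matter. The article, however, does spell out the terms of similarity, and training is not among them.
- **Training after the start.** Controls who train during follow-up would dilute even a comparison of changes. This is a different problem, which an entry criterion would not prevent, and the document gives no sign that it will happen.

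A reader might infer that trained controls could mask the effect of the course as a whole. The documents do not support this, because the primary results do not use controls. Nor do they support calling the controls matched: the text says only that they are similar.

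**Conclusion.** The asymmetry stands. As written, the protocol allows already-trained controls, and this can bias a year-after comparison of radiology applications, referrals and waiting times toward no difference. The point is confined to these secondary outcomes and to analyses that do not compare changes between groups.

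The size is unknown. The 1 − f shrinkage rests on an assumed share, an effect equal to that of the course and a year-after contrast; the power figures add an assumed control-group size and effect size. A reader might turn the 50% fall in referrals and test requests mentioned in the Introduction into an estimate of the bias. That figure comes from other studies and is not given as the effect of this training on a physician's yearly totals, so it cannot carry that estimate.

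**What to change.** - In section 2.2, apply to controls the same requirement of being untrained in clinical ultrasound that applies to participants.
- Record in both groups any ultrasound training outside the AECAP up to the end of follow-up, and report it descriptively.
- Keep all controls in the main analysis. If controls who trained later are left out, do so only in a labelled sensitivity analysis, because the exclusion selects on an event after baseline.

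The cost is one question at recruitment and one at the end of the study. The downside is a slightly smaller pool of eligible controls.
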